### Compliance

All tablets are provided to patients free of charge. Tablets will be administered with regular time intervals by a research nurse at the hospital or at home visits (Figure 1). Compliance will be assessed biweekly by phone-call or at clinical visits, where patients are asked how many days, if any, medication was not taken. Serum-amisulpride and serum-memantine will be measured by blood samples taken at the research department at 6 weeks and at end of treatment.

### Data Analysis

#### Primary Endpoint

The primary endpoint will be reduction in negative symptoms as measured with the negative symptom score from the Positive and Negative Syndrome Scale (PANSS) (78). Reduction in negative symptoms after 12 weeks of treatment: [PANSS negative baseline–PANSS negative at week 12]. PANSS negative assessments will be supplemented by Brief Negative Symptom Scale (BNSS) scores (57).

#### Secondary Endpoints

Secondary endpoints include changes in cognition (in particular working memory, learning and processing speed, and sustained attention), PANSS positive and total-scores, other clinical measures, level of functioning, adverse effects, and glutamate levels in the five *a priori* selected regions of interest mentioned above. Additionally, dopamine function in substantia nigra will be explored using NM-MRI techniques (37).

#### Exploratory Endpoints

Exploratory endpoints include associations between clinical data, quality of life, brain metabolites in other regions, e.g., ACC (33, 34), structural measures (e.g., hippocampus subfields) (35), diffusion data, and basal ganglia quantification (Table 2). Interactions between baseline brain metabolite levels and brain structure and white matter integrity in patients and HC will also be investigated.

### Planned Statistical Analyses

Homogeneity of variance between the two groups will be assessed using Levene’s test. Parametric data will be evaluated using parametric testing. Non-normally distributed data or data that exhibit unequal variances will be tested using non-parametric tests as appropriate. Fisher’s or χ2 exact tests will be used for group comparisons between categorical data. The Benjamini-Hochberg procedure will be used to control the type I error rate.

Data analyses on the primary outcome and most of the secondary outcomes will be performed before un-blinding and according to the per-protocol principle. Analyses of adverse events will be performed according to the intention-to-treat principle. Demographic variables and clinical characteristics will be reported in frequency for categorical data, and in mean values (with standard deviations and range) for normally distributed, continuous variables. Group comparisons for demographic data will be performed using independent *t*-tests for continuous variables and Chi-square tests for nominal and ordinal variables. Primary and secondary outcomes will be tested using repeated measures (rm)ANOVA.

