### Power Calculation

The power calculation is based on the primary outcome. We used the most representative clinical study we could identify and attempted to modify to the current setting. An 8-week RCT using risperidone plus memantine in stable schizophrenia patients (*N* = 40) reported a reduction in PANSS negative of −2.8 (SD 1.6) with memantine compared to −0.8 (SD 0.9) with placebo (79). Assuming a similar response, we expect add-on memantine to induce −2 ± 2 point more reduction in PANSS negative compared to amisulpride monotherapy. An *a priori* Student *t*-test (two-sided) with significance level α of 0.05 and a desired power (1-α) of 80%, shows that 16 completed patients in each arm is needed.

To increase power of secondary analyses, enrollment will continue until 18 participants in each arm have completed examinations. Moreover, AMEND will be extended to 12 weeks based on the median trial duration in the meta-analysis of add-on memantine [12 weeks (mean 11.5 weeks)] (42). Based on our center’s 20 years of experience with recruitment and treatment of antipsychotic-naïve patients, we expect an inclusion rate of 2 patients per month and an attrition rate of 25%. Thus, recruitment of 46 patients will take approximately 2 years.

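### The plan sends data with unequal variances to rank tests but also names rmANOVA unconditionally, so the primary test is not fixed, and a rank test does not remedy unequal variances

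*Protocol article*

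**What the plan says.** Three statements in the protocol article bear on how the primary outcome is tested.

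- **Variance check and switch (Planned Statistical Analyses).** "Homogeneity of variance between the two groups will be assessed using" Levene's test. Then: "Non-normally distributed data or data that exhibit unequal variances will be tested using non-parametric tests as appropriate". No unequal-variance parametric test is mentioned, and no outcome is exempted.
- **Named test (same section).** Primary and secondary outcomes are assigned to repeated measures ANOVA, with no condition attached.
- **Sizing (Power Calculation).** The source trial "reported a reduction in PANSS negative of −2.8 (SD 1.6) with memantine compared to −0.8 (SD 0.9) with placebo". From this, "we expect add-on memantine to induce −2 ± 2 point more reduction in PANSS negative compared to amisulpride monotherapy", and a two-sided Student t-test "shows that 16 completed patients in each arm is needed". For the secondary analyses, "enrollment will continue until 18 participants in each arm have completed examinations".

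Primary Endpoint defines the outcome as a single change score, baseline minus week 12, in PANSS negative. Randomization allocates 1:1 but does not hold the arm sizes equal.

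**The concern.** Used as a test of a location difference, a rank test assumes the same shape and spread in both arms under the null hypothesis. Unequal spread breaks that assumption too, so the stated remedy does not treat the stated problem. The usual answer is a test that allows unequal variances, such as Welch.

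The second difficulty is which sentence governs. With two time points and complete data, the group-by-time test of rmANOVA is the Student t-test on change, so the rmANOVA sentence and the power calculation agree with each other. The rank branch agrees with neither, because it does not test or estimate the 2-point mean difference on which the trial was sized. If the switching rule governs, the observed variances decide which hypothesis the primary p-value addresses. If the rmANOVA sentence governs, unequal variances are left untreated.

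**Working it through.** **Inputs.** Two-sided α 0.05, power 80%, difference 2, common SD 2, 16 needed and 18 targeted per arm, source-trial SDs 1.6 and 0.9 (all Power Calculation). Assumptions, because the article does not give them: Levene's test at 0.05 in both its mean- and median-centred forms, Mann-Whitney as the rank test, and normal changes unless stated.

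**1. The plan's own figure.** n = 2(z₀.₉₇₅ + z₀.₈)² × (SD/difference)² = 2(1.960 + 0.842)² × (2/2)² = 15.7, so 16 per arm. This reproduces the plan and shows that a common SD of 2 was used. (The exact t calculation gives 16.7, so 17, and 78.1% power at 16. The target of 18 covers this.)

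**2. Spread in the source trial.** SD ratio 1.6/0.9 = 1.78; variance ratio 2.56/0.81 = 3.16.

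**3. How often Levene's test rejects** (simulation, 40,000 replicates per setting).

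| Setting | Mean-centred | Median-centred |
|---|---|---|
| SD 1.6/0.9, 18 per arm | 55% | 48% |
| SD 1.6/0.9, 16 per arm | 50% | 42% |
| SD 1.6/0.9, 18 per arm, whole-point changes | 51% | 41% |
| SD 2/2, 18 per arm | about 6% | about 4% |

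With continuous changes, the rejection rate depends on the SDs only through their ratio.

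**4. Operating characteristics at 18 per arm, normal changes.** The two-stage rule means Mann-Whitney if Levene rejects and Student t (equivalent to rmANOVA) otherwise.

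| | Two-stage | Rank alone | Student t | Welch |
|---|---|---|---|---|
| Type I error, SD 1.6/0.9 | 5.0-5.1% | 5.4% | 5.3% | 5.1% |
| Power for 2 points, SD 1.6/0.9 | 99.0% | 98.9% | 99.4% | 99.4% |
| Power for 2 points, SD 2/2 | 82.7-82.8% | 80.4% | 83.0% | 82.9% |

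Now keep the SD ratio but set the average SD to 2. The root mean square of 1.6 and 0.9 is √[(2.56 + 0.81)/2] = 1.298. The scale factor is 2/1.298 = 1.541, which gives SDs of 2.47 and 1.39. Power is then about 79.6% for the two-stage rule and 81.8% for Welch.

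**5. Unequal arms.** Enrolment runs until each arm has 18 completers, so one arm can exceed 18. With 18 versus 22 (22 is an assumption), SDs 1.6/0.9 and the smaller arm more variable, type I error is about 5.8% for the two-stage rule, 5.9-6.0% for the rank test, 6.3-6.4% for Student t/rmANOVA and 4.9% for Welch. With the larger arm more variable, the two-stage rule gives about 4.1-4.2% and Welch 4.8%.

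**6. Skewed changes.** Take a shifted gamma with shape 1.5 (an assumption), equal means, SDs 1.6/0.9 and 18 per arm. Type I error as a test of means is about 11% for the rank test alone, 5.9% for Student t and 5.7% for Welch. The 11% belongs to the rank test, not to the whole rule. Levene's test rejects in 48% (mean-centred) or 32% (median-centred) of such trials. However, the switching sentence also sends non-normal data to rank tests, so skew can lead there by a second route.

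**The case against.** The strongest reply is that the article does name rmANOVA for the primary outcome, that the switching sentence ends with a qualifier leaving room for judgement, and that assumption checks are usually detailed in an SAP, which is not shown. The article also plans the primary analysis before unblinding, which limits choosing a test by treatment identity. The numbers support part of this reply: at the planned size with normal changes, the two-stage rule holds its error rate. With unequal arms and the smaller arm more variable, the rank test is also slightly nearer 5% than unconditional rmANOVA (5.9-6.0% against 6.3-6.4%).

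What remains is that the article states a rule, and the rule is wrong for unequal variances. Leaving detail to an SAP does not reconcile it with the rmANOVA sentence. The qualifier adds discretion to a data-driven choice, and coded groups still yield a p-value from each test.

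A reader might infer several stronger points that the document does not support:

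- **That the choice of test is a coin toss under the plan's own SDs.** The SDs of 1.6 and 0.9 belong to the cited 8-week trial in stable patients. The plan sized on a common SD of 2, under which the switch is rare.
- **That a rank test has no group-by-time form here.** The endpoint is a change score, which can be ranked directly.
- **That switching loses a baseline or stratum adjustment.** None is stated for the rmANOVA either.
- **That error rates should be judged with an arm well below 18.** Enrolment is meant to continue until both arms have 18 completers.

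**Conclusion.** The point holds as a fault of specification with modest numerical consequences. The switching rule, the rmANOVA sentence and the t-test sizing cannot all govern the primary outcome, and the rule's remedy for unequal variances is not one.

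The chance that Levene's test triggers the switch ranges from about 4-6% (common SD of 2) to about 48-55% (source-trial SD ratio) at 18 per arm. The document does not establish which applies. It assumes a response similar to the source trial but sizes on a single SD.

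With equal arms and normal changes, type I error stays near 5.1% and the power loss against Welch is about 2 points (81.8 − 79.6 = 2.2) even if the SD ratio is kept at an average SD of 2. Error rates drift when arms are unequal, and a rank test can mislead about means when changes are skewed. The main cost is that the primary hypothesis is not fixed in advance. The plan should be corrected, but the trial's conclusions would not be invalid without the correction.

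**What to change.** Remove Levene's test as a gate and name one primary analysis to be used whatever the variances:

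- **Preferred:** ANCOVA of week-12 PANSS negative, adjusted for baseline and the randomisation stratum (below 20 versus 20 or above), with heteroscedasticity-robust standard errors such as HC3.
- **If unadjusted:** Welch's test on the change score.

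State that this replaces both the switching sentence and the rmANOVA sentence for the primary outcome. Keep a rank or permutation test as a named sensitivity analysis, and apply the same rule to continuous secondary outcomes.

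The cost is a change of wording in the protocol, carried into the SAP. No new data are needed, since baseline score and stratum are already recorded. If the variances are in fact equal, the loss is trivial: at 18 per arm with SD 2 in both arms, Welch has 82.9% power against 83.0% for Student t.

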**FIGURE 1 F1:**
[figure not shown]
AMEND flow chart.

We hypothesize that add-on memantine to amisulpride will be superior to amisulpride monotherapy in reducing negative symptoms, and that this effect will correlate with thalamic glutamate levels. Moreover, we anticipate that add-on memantine will restore regional white matter integrity and improve cognitive functioning.

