### Randomization

The Hospital Pharmacy will be responsible for randomization, which will be conducted 1:1. Randomization will be stratified by PANSS negative sub-score, categorizing patients in either [Low PANSS negative baseline <20] or [High PANSS negative baseline ≥20].

The randomization will use permuted blocs in sizes of 4,6 and 8 to ensure an even distribution among the two groups. The number of patients in each group will not be restricted. In need of unblinding of a patient’s treatment, the pharmacy can be contacted at any time.

Intolerable side-effects or clinical worsening (defined as a 20% increase in PANSS positive subscale score compared to baseline PANSS positive score) will result in discontinuation of study treatment and study exclusion. Patients will be consulted with the senior consultant psychiatrist associated to the research project and further treatment will be initiated according to general treatment guidelines respecting the patients’ autonomy and requests.

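### The primary superiority test is fixed as per-protocol, leaving about 10 of 46 randomised patients outside it and open to bias of unknown direction and size

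*Protocol article*

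**What the plan says.** The hypothesis, stated under Figure 1 and in the Abstract, is that "add-on memantine to amisulpride will be superior to amisulpride monotherapy in reducing negative symptoms". The primary endpoint is the change "PANSS negative baseline–PANSS negative at week 12".

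Planned Statistical Analyses sets the efficacy population: "Data analyses on the primary outcome and most of the secondary outcomes will be performed before un-blinding and according to the per-protocol principle". The next sentence reserves the other principle for safety: "Analyses of adverse events will be performed according to the intention-to-treat principle". No efficacy analysis of all randomised patients is stated.

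The Randomization section describes how patients leave. Intolerable side effects or clinical worsening "will result in discontinuation of study treatment and study exclusion". Worsening is "defined as a 20% increase in PANSS positive subscale score compared to baseline PANSS positive score".

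Power Calculation sizes the trial on completers: 16 per arm are needed, and enrolment continues until 18 per arm have completed. On losses it says "we expect an inclusion rate of 2 patients per month and an attrition rate of 25" (per cent), with 46 patients to be recruited.

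**The concern.** Randomisation supports a superiority claim when patients are compared in the groups to which they were allocated. Here the compared groups are formed after randomisation, partly by events that an added active drug could plausibly change in either direction. If those events carry information about PANSS negative, and arise at a different rate or for different reasons in the two arms, the completers no longer differ by treatment alone. Enrolling until 18 per arm have completed restores the numbers but does not undo the selection. Analysing before un-blinding does not help either, because the losses come from what happened to the patients and not from who ran the analysis. At stake is the trial's single primary conclusion: a positive or a null result could each be challenged on these grounds.

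**Working it through.** **The plan's own figures.** Inputs from Power Calculation: difference 2, SD 2 (reading the stated ± 2 as an SD), two-sided α 0.05, power 80%.

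- Per arm: n = 2 × (1.960 + 0.842)² × 2² / 2² = 15.7, so 16. This reproduces the plan. The exact t calculation gives 78.1% power at 16, 80.7% at 17 and 83.0% at 18.
- Recruitment: 36 / 0.75 = 48 against the stated 46, a small gap. If 36 of 46 complete, 46 − 36 = 10 patients (22%) are outside the primary test.

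The article does not define the per-protocol set. I take non-completers to be outside it, since the endpoint needs a week-12 rating.

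**Bias.** Let d be an arm's dropout share and r the correlation between staying in the trial and a good outcome. The completers' mean then exceeds the mean of all randomised patients in that arm by

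shift = SD × r × φ(z_d) / (1 − d),

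where z_d is the normal quantile at d and φ the normal density. The bias is the difference between the two arms' shifts. Values of φ(z_d)/(1 − d) are 0.274 at d = 15%, 0.350 at 20%, 0.424 at 25%, 0.497 at 30% and 0.570 at 35%.

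Example: 35% against 15% with r = 0.5 gives 2 × 0.5 × (0.570 − 0.274) = 0.30 points.

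The documents give neither the split of dropout by arm nor r, so every row below is an assumption. Type I error comes from simulated trials with no true effect, SD 2 and a two-sided t-test. They used either 18 completers or 23 randomised per arm; where both were run for a scenario, they agree closely.

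| Dropout, arm A / arm B | Link r to outcome | Bias (points) | Type I error |
|---|---|---|---|
| 25% / 25% | same in both | 0 | 5% |
| 35% / 15% | none | 0 | 5% |
| 30% / 20% | 0.3 in both | 0.09 | 5.1% |
| 30% / 20% | 0.5 in both | 0.15 | about 5.6% |
| 35% / 15% | 0.3 in both | 0.18 | 6.1% |
| 25% / 25% | 0.3 in A, none in B | 0.25 | 6 to 7% |
| 35% / 15% | 0.5 in both | 0.30 | 7 to 7.5% |
| 35% / 15% | 0.7 in both | 0.41 | 10 to 11% |
| 25% / 25% | 0.7 in A, none in B | 0.59 | 15 to 16% |
| 25% / 25% | A loses exactly its worst quarter, B loses at random | 0.85 | 28% |

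The bias favours arm A, the arm with more or more selective loss. If A is memantine, the drug looks too good; if A is placebo, the same sizes count against it.

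**Power for all randomised patients.** If 25% drop out equally and get no drug benefit, a 2-point effect in completers becomes 0.75 × 2 = 1.5 points overall. At 23 per arm and SD 2 the power is about 70%.

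**The case against.** The strongest case on the other side concerns size. Both arms take amisulpride, and the Discussion reports that side effects in earlier add-on memantine trials did not differ from placebo, so a large imbalance is not to be presumed. The 25% is total attrition from the centre's experience, not loss through worsening or side effects. Worsening is defined on PANSS positive while the endpoint is PANSS negative, and their correlation is not given. All of this stands, and it makes the lower rows of the table possibilities rather than forecasts. It does not exclude imbalance: the Abstract says memantine has not been studied in first-episode psychosis.

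Three stronger readings are tempting and not supported.

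- A reader might infer that unequal dropout alone inflates the error rate. It does not: 35% against 15% with no link to outcome stays at 5%.
- A reader might take 0.85 points and 28% as the expected harm. That needs one arm to lose exactly its worst quarter and the other to lose patients at random, which nothing in the article suggests.
- Because Compliance says "Serum-amisulpride and serum-memantine will be measured by blood samples taken at the research department at 6 weeks and at end of treatment", a reader might infer that a low serum-memantine level removes patients from the memantine arm only. The article nowhere makes serum levels a criterion for the per-protocol set.

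It can also be said that the trial is labelled Phase I, has a mechanistic second aim, and may have an unseen analysis plan that adds an all-randomised analysis. The label and the second aim lower the stakes somewhat but do not justify per-protocol for a superiority claim. An unseen plan could add a sensitivity analysis, but this document already fixes which analysis is primary.

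**Conclusion.** The point holds as a fault in a stated rule, not as an omission. A superiority trial that expects to lose a quarter of its patients, some through treatment-related events, should not rest its primary test on the per-protocol set. The bias has no predictable direction and arises only if dropout is related to outcome and differs between arms in rate or mechanism. Against the 2-point target, the weak to moderate scenarios (about 0.1 to 0.3 points) amount to roughly 5 to 15%, and the strong ones (0.4 to 0.6 points) to 20 to 30%. These figures rest on SD 2, no true effect and assumed dropout patterns; the documents cannot narrow the range.

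**What to change.** 1. Make the primary analysis all randomised patients in their allocated arm. Use a likelihood-based repeated-measures model, or baseline-adjusted ANCOVA with multiple imputation, drawing on every available PANSS negative rating. Apply the same to the secondary efficacy outcomes now set as per-protocol.
2. In the Randomization section, separate stopping study treatment from leaving follow-up, for analysis purposes only, so that the planned week-12 PANSS negative rating is still collected where the patient consents. The discontinuation rule itself is not at issue here.
3. Add a sensitivity analysis for data not missing at random. The methods in step 1 assume missing at random by default and do not by themselves remove outcome-dependent dropout.
4. Keep per-protocol as supportive, with its set fixed before un-blinding.
5. Restate the power for the all-randomised analysis.

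The cost is revised wording, some extra follow-up ratings and moderate analysis work. The estimated effect may be smaller. If dropouts dilute it to 1.5 points, 23 per arm gives about 70% power, below the planned 80%, and the power statement should say so.

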#### Clinical Ratings

Symptom severity will be assessed by the Positive and Negative Syndrome Scale (PANSS) (46). Moreover, the primary clinical endpoint, PANSS negative symptoms, will be supplemented by the Brief Negative Symptom Scale (BNSS) (47). As descriptive and explorative endpoints, quality of life will be evaluated using the Quality of Life Scale (QLS) (48). The UKU side effect rating scale (49) and Changes in Sexual Functioning Questionnaire (CSFQ) (50) will be used to asses potential side-effects. Handedness will be assessed with Edinburgh Handedness Inventory (EHI) (51). Level of functioning will be evaluated with the Personal and Social Performance Scale (PSP) (52), and Global Assessment of Functioning (GAF) (53). The Clinical Global Impression (CGI) (54) will be used to assess the patients’ overall illness severity.

Based on previous studies in similar patient populations we expect the mean PANSS negative symptom score to reside around 20, eg. (9, 55) and in order to enhance generalizability to this patient population, we did not set a minimal level of symptoms.

In order to retain comparability to other studies, e.g.,(42–44) we opted for PANSS. To address the controversy regarding of PANSS negative symptoms, we employ BNSS as secondary endpoint. We recently validated BNSS for use in Danish settings (56, 57).

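### The named primary test, repeated-measures ANOVA on baseline and week 12, is valid but conservative under the baseline-stratified randomisation; adjusting for baseline PANSS negative recovers power if the pre/post correlation is low to moderate

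*Protocol article*

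**What the plan says.** Under Planned Statistical Analyses, the protocol article names one test for efficacy: "Primary and secondary outcomes will be tested using repeated measures (rm)ANOVA". It mentions no baseline covariate and no stratum term.

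Under Primary Endpoint, the outcome is "Reduction in negative symptoms after 12 weeks of treatment", written as "PANSS negative baseline–PANSS negative at week 12". Two time points define it.

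Under Randomization: "Randomization will be stratified by PANSS negative sub-score", with a cut at 20. Allocation is 1:1, and "The randomization will use permuted blocs in sizes of 4,6 and 8". Under Clinical Ratings, "we expect the mean PANSS negative symptom score to reside around 20", so the cut falls near the centre of the expected distribution.

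Power Calculation uses a two-sided Student t-test at 5% and 80% power, with an expected effect of "2 ± 2 point more reduction in PANSS negative compared to amisulpride monotherapy" (printed with a minus sign before the first 2). It gives 16 completers per arm, and enrolment continues to 18.

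**The concern.** The stratification factor is the primary endpoint's own baseline, cut in two. Change is normally correlated with baseline, so stratifying on it makes the treatment comparison more precise. An unadjusted analysis of change does not use that gain: its standard error is computed as if baseline had been left to chance. The confidence interval for the primary effect is then wider than the design warrants, and some power is lost. In a trial planned for 36 completers, an adjustment that uses only a baseline already measured deserves attention.

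**Working it through.** **1. The plan's own figure.** Inputs from Power Calculation: difference 2, SD 2, two-sided alpha 0.05, power 80%.

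n per arm = 2 × (1.960 + 0.842)² × (2/2)² = 15.7, so 16. The stated figure reproduces. The exact noncentral t gives 17 (power 78.1% at 16 and 83.0% at 18).

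**2. What the named test is.** With two time points, the group-by-time F is the square of the two-sample t on change. The analysis and the sample size therefore rest on the same unadjusted comparison.

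**3. Variance.** Let σ be the SD of PANSS negative at each visit (taken as equal) and ρ the pre/post correlation.

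- Variance of change: 2σ²(1 − ρ)
- Residual variance after ANCOVA on baseline: σ²(1 − ρ²)
- Ratio: (1 + ρ)/2, which is 0.65, 0.75, 0.85 and 0.95 at ρ = 0.3, 0.5, 0.7 and 0.9

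Fixing the SD of change at 2 ties σ to ρ: σ = 2/√(2(1 − ρ)). The article gives neither, so both are ranged as assumptions.

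**4. Why the test is conservative.** Baseline explains a share (1 − ρ)/2 of the variance of change. For a normal baseline, a cut at the mean captures 2/π ≈ 0.64 of that share. At ρ = 0.5 this is 0.25 × 0.64 = 0.16. With strata balanced, the true standard error is √(1 − 0.16) = 0.917 of the one the test uses. The nominal cut-off becomes 1.96/0.917 = 2.14, a two-sided error of about 3.2%.

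**5. Simulation.** 36 completers, baseline mean 20, two strata cut at 20, permuted blocks of 4, 6 and 8 within stratum, SD of change 2, effect 0 or 2. Each cell has 10,000 to 40,000 runs.

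| ρ | Implied σ | Type I, rmANOVA | Type I, ANCOVA (baseline) | Power, rmANOVA | Power, ANCOVA (baseline) | Power, ANCOVA (baseline + stratum) |
|---|---|---|---|---|---|---|
| 0.3 | 1.7 | 2.8% | 4.9% | 85.4% | 94.3% | 93.8% |
| 0.5 | 2.0 | 3.3% | 4.9% | 84.5% | 92.0% | 91.4% |
| 0.7 | 2.6 | 4.1% | 5.2% | 84.0% | 88.0% | 87.2% |
| 0.78 | 3 | 4.3% | 5.0% | 83.8% | 86.6% | 85.9% |
| 0.875 | 4 | 4.5% | 5.0% | 83.4% | 84.9% | 84.0% |
| 0.9 | 4.5 | 4.6% | 4.9% | 83.2% | 84.5% | 83.7% |
| 0.92 | 5 | 4.8% | 5.0% | 83.4% | 84.0% | 83.3% |
| 0.96 | 7 | 4.8% | 5.0% | 83.2% | 83.3% | 82.3% |

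A repeat run gave rmANOVA type I error of 2.8%, 3.2% and 4.1% at ρ = 0.3, 0.5 and 0.7. Adding the stratum to continuous baseline costs 0.5 to 1 point in every row. The gain comes from the baseline covariate.

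**6. If the SD of change exceeds 2.** At a given σ, a larger SD of change means a lower ρ. With the effect still 2 and 18 per arm, rmANOVA against baseline ANCOVA gives:

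- σ = 4: 29% against 38% (ρ = 0.5); 46% against 52% (ρ = 0.7)
- σ = 5: 19% against 27%; 31% against 36%
- σ = 6: 14% against 20%; 24% against 28%

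The simulation treats the 36 completers as the randomised set. With the 25% attrition the article expects, balance within strata would be somewhat looser and the conservatism somewhat smaller.

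**The case against.** The strongest reply is that nothing here is inconsistent. The endpoint is a change, the sizing test is a t-test on change, and rmANOVA matches both. On the plan's own inputs, 18 per arm already exceeds 80% power. That stands: this is a question of efficiency.

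The size is also fairly contested. With the SD of change at 2, correlations of 0.3 to 0.7 imply a spread of only 1.7 to 2.6 points in PANSS negative, which looks narrow for a trial that sets no minimum symptom level. At a spread of 5 or more the gain disappears. That stands as well, within limits. The planning figure of 2 draws on SDs of 1.6 and 0.9 from stable patients over 8 weeks, whereas this trial enrols never-treated patients starting amisulpride and follows them for 12 weeks. If their change varies more, the correlation falls at a given spread and the relative gain grows.

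Four stronger readings are tempting, but the document does not support them.

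- **That the planned test inflates false positives.** Its error rate stays below 5% in every row.
- **That the plan rules out adjustment.** A condensed article that names no covariate does not exclude one, and an analysis plan that is not shown may add it. The point rests on the test that is named and the unadjusted sizing.
- **That rmANOVA needlessly loses patients with missing visits.** The endpoint uses two visits, the primary analysis is per protocol, and ANCOVA of week 12 would lose the same patients without a week-12 score.
- **That intermediate visits would blur the week-12 contrast.** The endpoint definition brings in no intermediate visit.

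**Conclusion.** The point holds as an efficiency finding. The named test is valid but conservative, and it does not use the baseline on which the trial stratifies. With 18 per arm and an SD of change of 2, the power given up is about 8 points at a correlation of 0.3, 7 at 0.5, 3 to 4 at 0.7, and about 1 or less from 0.9 upwards (a baseline SD of about 4.5 or more). These figures assume normal scores with equal variance at both visits, and a correlation that the article does not state. No single value in this range can be called the likely one. The case for changing rests on asymmetry: baseline adjustment costs almost nothing where the correlation is very high, and it helps most where the planning SD proves too small.

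**What to change.** Name as primary analysis an ANCOVA of week-12 PANSS negative on treatment and continuous baseline PANSS negative. The randomisation stratum is optional: it adds no power once baseline is in the model. A mixed model with the same terms, reporting the week-12 treatment contrast, is an equal alternative. Report the adjusted mean difference with its 95% confidence interval. Use the same form, with each outcome's own baseline, for continuous secondary outcomes.

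If rmANOVA is kept, state that group-by-time is the tested term and include the stratification factor. In the simulation this brings type I error to about 5% and gives power of 91%, 89% and 86% at ρ = 0.3, 0.5 and 0.7, which is part of the ANCOVA gain.

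The cost is a wording change before unblinding. No new data are needed. The statistical price is one or two degrees of freedom, at most about 1 power point at very high correlation when the stratum is also included.
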